#### Secondary outcomes

Repeated measure two-factor analysis will be used to analyze the difference and mean change among baseline, 4 and 8 weeks, difference and mean change between groups, and interaction between groups and observed time. For dichotomous outcomes, the *χ*^2^ test or logistic regression will be used. For the comparison of adverse events (AEs) between groups, the *χ*^2^ test or Fisher’s exact test will be performed.

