**Methods/design:**

A two-center, randomized, waitlist-controlled trial will be carried out to evaluate whether acupuncture treatment improves FD symptoms. Seventy six participants aged 18 to 75 years with FD as diagnosed by Rome III criteria will be recruited from August 2013 to January 2014 at two Korean Medicine hospitals. They will be randomly allocated either into eight sessions of partially individualized acupuncture treatment over 4 weeks or a waitlist group. The acupuncture group will then be followed-up for 3 weeks with six telephone visits and a final visit will be paid at 8 weeks. The waitlist group will receive the identical acupuncture treatment after a 4-week waiting period. The primary outcome is the proportion of responders with adequate symptom relief and the secondary outcomes include Nepean dyspepsia index, EQ-5D, FD-related quality of life, Beck’s depression inventory, state-trait anxiety inventory questionnaire, and level of ghrelin hormone. The protocol was approved by the participating centers’ Institutional Review Boards.

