However, previous studies have reported inconsistent findings of the clinical benefit of acupuncture treatment for FD [4,19]. Nevertheless, these studies have been criticized for adopting relatively sub-optimal acupuncture treatment, i.e., three times a week for 2 weeks [19,20], or testing a less generalizable treatment regimen, i.e., daily acupuncture treatment for 4 weeks [4]. According to a systematic review by Zhu [21], the acupuncture treatment for FD lacks high-quality evidence. Hence, it was addressed that randomized clinical trials corresponding with the CONSORT statement and STandards for Reporting Interventions in Clinical Trials of Acupuncture (STRICTA) recommendations have to be implemented to evaluate the efficacy of acupuncture for FD. In addition, considering the questions which have been raised so far on the adequacy of various sham acupuncture controls [22,23], care should be taken before simply adopting any available sham devices or procedures in the early phase.

Given that FD is now regarded as a complex disorder of which the pathophysiological mechanisms are inconclusive [24], various factors are likely to come into play. Among them, ghrelin, an orexigenic peptide, has been shown to play an important role in gastric motility, food intake, and potential gastroprotection against acute gastric mucosal injury [25,26]. However, it is yet to be studied whether ghrelin is associated with the mechanisms of acupuncture treatment in patients with FD [27,28].

Taken together, we felt the need to properly test whether acupuncture treatment would help symptom improvement in FD patients and, subsequently, the related mechanism. Therefore, we propose a two-center, randomized, waitlist-controlled trial investigating the effectiveness of acupuncture for symptom improvement in patients with FD and to assess whether the change in ghrelin secretion is associated with acupuncture treatment.

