## Methods/design

### Objectives

The aims of this study are to: i) assess the effect of acupuncture treatment on patients with FD in comparison with waitlist group with respect to adequate symptom relief and ii) to elucidate whether ghrelin level is associated with clinical effect of acupuncture.

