##### Ghrelin measurement (total ghrelin and deacylated ghrelin)

Ghrelin is mostly secreted by endocrine cells in the oxyntic mucosa of the stomach [40,41] and is present in the peripheral circulation as two subtypes: acylated and unacylated [42]. Its physiologic functions include regulating food intake [43,44] and secretion of gastric acid [45], accelerating gastric emptying [46], and stimulating gastric motility [47,48]. In our study, approximately 6 mL of whole blood, 3 mL each for total and unacylated ghrelin, will be collected on an empty stomach at baseline and at 4 weeks. The total and unacylated ghrelin assay will be performed using the commercially available radioimmunoassay and enzyme-linked immunosorbent assay kits.

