### Statistical analysis

A statistical analysis will be performed by an independent statistician who is blinded to group allocation using SPSS 21.0 (IBM SPSS Statistics, New York, USA). Our independent statistician will have an access to the final dataset which will be kept locked so that investigators will have limited access. All data will be presented as means and standard deviations or number (%), and all analyses will be based on an intention-to-treat principle. For intention-to-treat analysis, the last observation carried forward rule will be applied. The statistical significance level will be set at 0.05 (two-sided), with the 95% confidence intervals.

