## Discussion

To our knowledge, acupuncture treatment for FD has not been intensively investigated. This article describes the protocol of a randomized trial with a waitlist control group to evaluate the effectiveness of usual acupuncture practice for FD patients in Korea. We expect that the results will be able to answer whether acupuncture treatments help adequate symptom improvement and quality of life, and whether ghrelin secretion is associated with acupuncture treatment, compared with the no acupuncture group.

A placebo control group is essential to determine the efficacy of a new treatment. Given that there exist some published sham-controlled trials of acupuncture for FD [4,19], some may argue that a sham acupuncture control should be adopted to investigate specific effect of acupuncture. However, it is yet to be clearly understood what specific components of acupuncture treatment work in the perceived therapeutic effect of acupuncture [50]. Sham controls used in the previous studies included superficial needling at non-acupuncture points with [4] or without electrical stimulation [19]. In our view, none of them are inert, and we could not find any rationale for a better choice of sham control for our study. Non-pharmacological intervention studies pose particular challenges to identify inactive control groups that generate expectancy comparable to the study intervention [20]. Thus, participants in the non-pharmacological intervention studies are often randomly allocated to waitlist control condition as a comparison to the treatment modality of interest. In this context, we decided to conduct a waitlist controlled trial as a starting point. From this trial, we can investigate how acupuncture might work against a group without acupuncture treatment. As natural fluctuations of symptoms in the disease process and high placebo response are unique challenges in FD trials, we can also obtain valuable information for further studies on how acupuncture treatment will affect symptoms of FD during the treatment and over a month of follow-up against a waitlist control. Additionally, a minimum treatment duration of 4 weeks that reflects the symptom periodicity is recommended for a treatment trial for functional gastrointestinal disorders [20]. Therefore, this will be the first Korean randomized controlled trial testing the adequate acupuncture intervention in terms of duration and reflecting everyday practice.

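### The ghrelin aim is worded as two different questions, and the one analysis stated for continuous secondary outcomes fits only one of them and names a visit at which ghrelin is not sampled

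*Protocol article*

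**What the plan says.** Ghrelin is a secondary outcome: the abstract's list ends with "state-trait anxiety inventory questionnaire, and level of ghrelin hormone". The article describes its purpose in three places.

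- Objectives, aim ii: "to elucidate whether ghrelin level is associated with clinical effect of acupuncture".
- Background, last paragraph: "to assess whether the change in ghrelin secretion is associated with acupuncture treatment".
- Discussion, first paragraph: "whether ghrelin secretion is associated with acupuncture treatment, compared with the no acupuncture group".

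On timing, the ghrelin measurement section says that blood "will be collected on an empty stomach at baseline and at 4 weeks". Table 2 agrees: it marks two blood collections for ghrelin and none at 8 weeks.

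On analysis, the Secondary outcomes paragraph under Statistical analysis gives one method for continuous measures: "Repeated measure two-factor analysis will be used to analyze the difference and mean change among baseline, 4 and 8 weeks", followed by "difference and mean change between groups, and interaction between groups and observed time". It makes no separate provision for ghrelin and has no term linking ghrelin to a clinical outcome.

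**The concern.** Two questions are in play. One is whether acupuncture changes ghrelin, which is a contrast between arms. The other is whether participants whose ghrelin changes more also improve more, which is an association between two variables measured in the same people. The Objectives ask the second; the Background and Discussion ask the first.

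The stated analysis addresses the first only. If it is followed as written and reported under aim ii, a ghrelin difference between arms could be read as showing that ghrelin is tied to symptom relief when the data say nothing of the kind. Conversely, a null difference between arms could hide a real association. This is one of only two stated aims, and the abstract presents the trial as informative about mechanism.

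The three-visit description also does not fit an outcome measured twice. That is a smaller matter, but the article should settle it.

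**Working it through.** **Side-by-side reading**

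| Item | Section | Content |
|---|---|---|
| Aim ii | Objectives | ghrelin against clinical effect: association |
| Ghrelin question | Background | ghrelin change against treatment: arm contrast |
| Ghrelin question | Discussion | ghrelin against treatment, relative to no acupuncture: arm contrast |
| Sampling times | Ghrelin measurement; Table 2 | 2 (baseline, week 4) |
| Analysis times | Statistical analysis, Secondary outcomes | 3 (baseline, weeks 4 and 8) |
| Analysis terms | same paragraph | group, time, group by time |

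Cut down to two times, the group-by-time interaction is the same test as a two-sample *t*-test on change from baseline. The method can therefore still be run on ghrelin, but what it estimates remains a difference between arms.

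**The plan's own figure.** The sample size serves the primary outcome and is used here only for a realistic number of completers. With p_t = 0.60, p_c = 0.25 and mean 0.425:

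n = (1.960 × √(2 × 0.425 × 0.575) + 0.842 × √(0.24 + 0.1875))² / 0.35² ≈ 30.1 per arm.

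This agrees with the article. With 20% dropout, 30.1 / 0.8 = 37.6, rounded up to 38 per arm and 76 in total, which also agrees.

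**Do the two questions come apart?** The simulation used 30 completers per arm, standardised change scores, a clinical difference between arms of 0.8 SD, two-sided 5% tests and 4,000 runs per scenario. All effect sizes are assumptions.

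| Scenario | Group by time on ghrelin | Association, treated arm | Association, both arms, arm-adjusted |
|---|---|---|---|
| Ghrelin arm difference 0.8 SD, within-arm correlation 0 | 87% | 5% | 5% |
| No ghrelin arm difference, within-arm correlation 0.5 | 5% | 82% | 99% |

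Hand checks on the high entries:

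- Arm contrast: 0.8 × √(30/2) = 3.10; Φ(3.10 − 2.00) ≈ 0.86.
- Association in the treated arm: atanh(0.5) × √(30 − 3) = 0.549 × 5.196 = 2.85; Φ(2.85 − 1.96) ≈ 0.81.
- Association in both arms, one more degree of freedom spent on arm: 0.549 × √(60 − 4) = 4.11; Φ(4.11 − 1.96) ≈ 0.98.

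The entries near 5% are the nominal error rate. In each scenario the stated test and the association test point in opposite directions.

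**The case against.** The strongest reply is that this is a condensed article. Its secondary-outcome paragraph is generic, and an exploratory correlation between ghrelin change and response is commonly left to an analysis plan, which is not shown here. Two of the three statements of the ghrelin question are arm contrasts, which the printed method answers. The time mismatch also has an easy reading: analyse each outcome at the visits where it was measured. Finally, the Discussion already cautions that ghrelin changes may not fully account for symptom improvement.

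Much of this stands. A reader might infer that aim ii will get no valid answer. The document cannot show that, because an unseen plan may contain an association analysis.

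A reader might also combine the three-visit model with the rule "For intention-to-treat analysis, the last observation carried forward rule will be applied" and conclude that every participant's week-4 ghrelin would be copied into week 8. That is strained. The rule concerns missing data in the intention-to-treat analysis, and a week-8 ghrelin value is never scheduled, so it is not missing.

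Nor should the size of the problem be expressed as a smallest detectable correlation. The documents give no ghrelin effect or correlation and claim no power for this aim, so such a figure would describe a proposed analysis rather than the fault.

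What the reply does not remove is the conflict within the printed text. An added association analysis elsewhere would leave the Objectives at odds with the Background and Discussion, and the stated visits at odds with the sampling schedule. The Discussion's caution supplies no test of the link.

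**Conclusion.** The point holds as an inconsistency in the stated aim, together with a stated analysis that matches only one of its two meanings and names a visit without ghrelin data. The aim mismatch is the part that matters; the visit mismatch is secondary.

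The size cannot be given as a single figure from the documents. The simulation shows only that the two questions can give opposite answers at about the planned number of completers (87% against 5% one way, 5% against 82% or 99% the other), under assumed effects. The primary comparison and its sample size are untouched. The finding is worth acting on because it affects one of two aims and the remedy costs almost nothing.

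**What to change.** 1. Use one wording of the ghrelin aim in the Background, Objectives and Discussion.
2. State that total and unacylated ghrelin are analysed from baseline and week 4 only, outside the three-visit model, by comparing arms at week 4 with adjustment for baseline ghrelin and hospital (randomisation is carried out within hospital).
3. If the Objectives wording stays, prespecify an exploratory analysis relating baseline-to-week-4 ghrelin change to clinical response, with arm in the model, and report the estimate with its 95% confidence interval. Clinical response can be responder status or change in a symptom score, named in advance. If the wording does not stay, reword aim ii as the arm contrast and do not present an arm difference in ghrelin as evidence that ghrelin is linked to symptom relief.

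The cost is a few sentences and a small additional analysis of data already being collected, with no extra samples, visits or participants.

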#### Data management

To promote data quality, the data will be collected by well-trained assessor and the double entry of the data will be implemented by clinical research coordinators.

### Safety

We will perform the following tests on all participants at screening: white blood cell count, hemoglobin, hematocrit, platelet, aspartate aminotransferase/alanine aminotransferase, gamma-glutamyl transpeptidase, blood urea nitrogen, creatinine, and erythrocyte sedimentation rate. These tests will help us to exclude participants who have serious diseases and abnormal liver, heart, kidney, or other organ function.

Participants will be asked about AEs at each clinic visit and during the 4-week telephone interviews. AEs will be defined as any unexpected and unfavorable signs, symptoms, or diseases temporally associated with acupuncture treatment. If any AEs occur, the appropriate treatment will be provided to the participant immediately. During the entire study, AEs will be recorded in the dedicated document including its severity and causality which will then be reviewed by the independent monitor.

Any serious AEs that are life-threatening or result in hospitalization, death, or significant or persistent disability will be promptly reported to the clinical research associate within 24 h from the time of recognition.

### Quality control

As we do not expect serious safety concerns, outstanding benefit, or futility in this study, no official Data Monitoring Committee will be established in each hospital. Instead, to retain the accuracy and quality of the clinical trial, the clinical research associate will conduct regular monitoring by checking investigator study files, informed consent forms, case report forms, compliance with treatments, serious AEs, and data records.

### Ethical approval and registration

This trial will be carried out according to the standards of the International Committee on Harmonization on Good Clinical Practice and the revised version of the Declaration of Helsinki. Institutional review boards at Kyung Hee University Korean Medicine Hospital and Kyung Hee University Hospital at Gangdong, have approved an initial version of this protocol (KOMCIRB 2013–05 for Kyung Hee University Korean Medicine Hospital and KHNMC-OH-IRB 2013–006 for the Kyung Hee University Hospital at Gangdong) on 28 June and 29 July 2013, respectively. This trial is registered in the ClinicalTrials.gov (NCT01921504). In addition, all investigators were trained to maintain the personal information of study participants and signed a pledge to protect the confidentiality of participants.

## Discussion

To our knowledge, acupuncture treatment for FD has not been intensively investigated. This article describes the protocol of a randomized trial with a waitlist control group to evaluate the effectiveness of usual acupuncture practice for FD patients in Korea. We expect that the results will be able to answer whether acupuncture treatments help adequate symptom improvement and quality of life, and whether ghrelin secretion is associated with acupuncture treatment, compared with the no acupuncture group.

A placebo control group is essential to determine the efficacy of a new treatment. Given that there exist some published sham-controlled trials of acupuncture for FD [4,19], some may argue that a sham acupuncture control should be adopted to investigate specific effect of acupuncture. However, it is yet to be clearly understood what specific components of acupuncture treatment work in the perceived therapeutic effect of acupuncture [50]. Sham controls used in the previous studies included superficial needling at non-acupuncture points with [4] or without electrical stimulation [19]. In our view, none of them are inert, and we could not find any rationale for a better choice of sham control for our study. Non-pharmacological intervention studies pose particular challenges to identify inactive control groups that generate expectancy comparable to the study intervention [20]. Thus, participants in the non-pharmacological intervention studies are often randomly allocated to waitlist control condition as a comparison to the treatment modality of interest. In this context, we decided to conduct a waitlist controlled trial as a starting point. From this trial, we can investigate how acupuncture might work against a group without acupuncture treatment. As natural fluctuations of symptoms in the disease process and high placebo response are unique challenges in FD trials, we can also obtain valuable information for further studies on how acupuncture treatment will affect symptoms of FD during the treatment and over a month of follow-up against a waitlist control. Additionally, a minimum treatment duration of 4 weeks that reflects the symptom periodicity is recommended for a treatment trial for functional gastrointestinal disorders [20]. Therefore, this will be the first Korean randomized controlled trial testing the adequate acupuncture intervention in terms of duration and reflecting everyday practice.

One of the crucial limitations of this study is that the doctors and participants cannot be blinded to the group allocation. Blinding refers to keeping key persons, such as participants, healthcare providers, outcome assessors, and data analysts, unaware of the treatment administered or of the true hypothesis of the trial [51,52]. Although all outcome measures will be administered and collected by the blinded nurse to minimize the risk of detection bias, and a statistician blind to group assignment will perform analysis of the data, the problem of participant unblinding still remains. We will carefully discuss residual sources of bias and their potential impact on clinical outcomes when we analyze the study findings and prepare for publication.

Some may argue that selection of ghrelin as a target mechanism may provide limited evidence. We understand that a variety of factors have been suggested to be associated with pathophysiology of FD [24-26]. Among many, ghrelin has been shown to play an important role in gastric motility, food intake, and potential gastroprotection against acute gastric mucosal injury [25,26]. However, to our best knowledge, there is no report on how ghrelin is related to acupuncture treatment for FD. Changes in ghrelin level after acupuncture, therefore, may not completely explain how acupuncture might work for symptom improvement in patients with FD. Nevertheless, ghrelin can be one of the many possible factors underlying the mechanism of acupuncture for FD and this study will help add evidence on this.

## Trial status

This study is currently recruiting participants. No interim analyses are planned and the primary results will be published by 2015.

## Abbreviations

AEs: Adverse events; AMSRC: Acupuncture and Meridian Science Research Center; BDI: Beck’s depression inventory; CV: Conception Vessel; EQ-5D: European quality of life-5 dimension; EX-HN: Extra acupoint of Head and Neck; FD: Functional dyspepsia; FD-QoL: Functional dyspepsia-related quality of life; GB: Gallbladder; LI: Large Intestine; NDI-K: Nepean dyspepsia index – Korean version; PC: Pericardium; PR: Proportion of responders; QoL: Quality of life; SI: Small Intestine; ST: Stomach; STAI: State-trait anxiety inventory; STRICTA: STandards for Reporting Interventions in Clinical Trials of Acupuncture; VAS: Visual analogue scale.
